## Abstract

**Background:**

Even in the current drug-eluting stent era, revascularization for coronary stenosis with fractional flow reserve (FFR) between 0.75 and 0.80, the so-called “gray zone,” is a matter of debate. Previous studies have reported conflicting results regarding outcomes of revascularization versus deferral for coronary stenosis when FFR values are in the gray zone, but these studies have had differing designs and populations. We therefore will investigate whether medical therapy plus percutaneous coronary intervention (PCI) is superior to medical therapy alone in reducing major cardiovascular events in patients presenting with coronary stenosis with gray zone FFR values.

**Methods/design:**

This is a prospective, multicenter, open-label, parallel group, randomized, controlled, superiority study. A total of 410 eligible participants will be recruited and randomized to either the medical therapy plus PCI group or the medical therapy alone group. The primary endpoint is 1-year major adverse cardiac events (MACEs), defined as a combined endpoint of all-cause death, nonfatal myocardial infarction (MI), or unplanned target vessel revascularization (TVR). Secondary endpoints include MACE at 2 and 5 years. Moreover, each individual component of the primary endpoint, cardiovascular death, target vessel-related and non-target vessel-related MI, all MI, clinically driven TVR or non-TVR, all revascularization, stent thrombosis, and angina symptom status will be evaluated at 1, 2, and 5 years.

**Discussion:**

This is the first prospective, multicenter, randomized, controlled study to investigate the superiority of medical therapy plus PCI over medical therapy by itself in reducing major cardiovascular events in patients presenting with coronary stenosis with “gray zone” FFR values. The results will help interventional cardiologists in making revascularization decisions regarding coronary stenosis with gray zone FFR values.

**Trial registration:**

University Hospital Medical Information Network Clinical Trials Registry, UMIN000031526. Registered on 1 March 2018.

**Electronic supplementary material:**

The online version of this article (10.1186/s13063-019-3182-1) contains supplementary material, which is available to authorized users.

## Background

Coronary physiological assessment can more effectively guide management decisions on intermediate coronary stenotic lesions than coronary anatomical assessment. This allows determination of whether the patient would benefit from revascularization or medical therapy.

Fractional flow reserve (FFR) is an established invasive index for determination of the functional severity of a coronary stenosis. FFR values < 0.75 were shown to be associated with inducible myocardial ischemia with > 99% positive predictive value [1]. The DEFER study (Deferral versus performance of percutaneous coronary intervention (PCI) of functionally non-significant coronary stenosis) has since demonstrated that PCI can be safely deferred in coronary stenosis with FFR ≥ 0.75 [2]. In addition, at 15-year follow-up, it was reported that the rate of myocardial infarction (MI) was significantly lower in the deferred group than in the revascularization group (2.2% versus 10%) [3]. On the contrary, PCI for coronary stenosis with FFR ≤ 0.80, compared with medical therapy by itself, is associated with improved clinical outcomes [4–8]. Nonetheless, revascularization for coronary stenosis with FFR between 0.75 and 0.80, the so-called gray zone, is still an unresolved issue. Owing to differing study designs and populations, previous studies have reported conflicting results regarding outcomes of revascularization versus deferral for coronary stenosis with gray zone FFR values [9–17].

We therefore will conduct a prospective, multicenter, randomized, controlled trial to investigate whether medical therapy plus PCI is superior to medical therapy alone in reducing major cardiovascular events in patients presenting with coronary stenosis with gray zone FFR values.

## Methods/design

### Study design

The Comparison of clinical outcomes following percutaneous coronary intervention versus optimal medical therapy based on gray zone fractional flow reserve in stable angina patients with intermediate coronary artery stenosis (COMFORTABLE) study is designed as a prospective, multicenter, open-label, parallel group, randomized, controlled, superiority study. This study is being conducted across 11 hospitals in Wakayama Prefecture and Tokyo, Japan. A total of 410 eligible participants will be recruited and randomized into either the performed PCI group or the deferred PCI group, with an allocation ratio of 1:1. Recruitment will begin soon.

The protocol structure was written in compliance with the Consolidated Standards of Reporting Trials (CONSORT) 2010 statement guidelines, and it follows the Standard Protocol Items: Recommendations for Interventional Trials (SPIRIT) 2013 statement. Figure 1 shows the CONSORT diagram of this study, and Fig. 2 shows the SPIRIT schedule. The complete SPIRIT checklist for the study is provided in Additional file 1.

**Fig. 1 Fig1:**
[figure not shown]
CONSORT diagram. *PCI* Percutaneous coronary intervention

**Fig. 2 Fig2:**
[figure not shown]
SPIRIT schedule of enrollment, intervention, and assessments. *If clinically indicated. *FFR* Fractional flow reserve, *PCI* Percutaneous coronary intervention

### Objective

The aim of this study is to determine whether medical therapy plus PCI is superior to medical therapy by itself in reducing major cardiovascular events in patients presenting coronary stenosis with “gray zone” FFR values.

### Participants

Participants will be eligible for registration in this study if they meet all of the inclusion criteria and none of the exclusion criteria listed in the subsections below.

#### Inclusion criteria

Intermediate coronary stenosis presenting with an FFR between 0.75 and 0.80Aged ≥ 20 yearsAble to provide written informed consent prior to any study-specific procedures

#### Exclusion criteria

Culprit vessel in acute coronary syndromeUntreated significant lesions (percentage of diameter stenosis > 70% and/or FFR < 0.75) in coronary arteries other than the target vesselUnstable hemodynamicsHemodialysisPrevious coronary artery bypass grafting (CABG)Allergy to antiplatelet therapy, anticoagulants, or contrast mediumIntracranial and/or gastrointestinal bleedingPlanned surgical procedure within 12 monthsLife expectancy < 1 yearPregnancySevere valvular heart diseaseParticipation in clinical trials of other devices or drugsLeft main coronary artery (LMCA) disease (percentage of diameter stenosis > 50%) or planned PCI for LMCA diseaseChronic total occlusionsHeavily calcified or tortuous vessels, meaning inability to cross the lesion with a pressure wire is expectedDiffuse diseases, heavily calcified lesions, small vessels, and/or aneurysmal lesions, meaning PCI is thought to be unsuitable by operators

### Randomization

Eligible participants will be allocated to one of the two groups (medical therapy plus PCI group or medical therapy alone group) by the online randomization system. Balanced randomization based on critical variables (diabetes, age, sex, and institution) will be performed automatically by the randomization algorithm. Knowledge of the treatment allocation is open to the investigators and participants.

### Sample size calculation

On the basis of event rates of previous studies that evaluated deferred versus performed revascularization in patients presenting coronary stenosis with gray zone FFR values, we predicted that the event rates at 1 year would be 6.4% in the revascularization group and 16% in the deferred group [15]. Under the above event rates and the hypothesis that the crossover rate from the medical therapy alone arm to the PCI arm is 5%, we calculated that a sample size of 368 patients (184 per arm) would provide the trial with 80% power to detect the superiority of medical therapy plus PCI over medical therapy by itself, at a two-sided alpha level of 5%. Assuming a dropout rate of 10% (patients lost to follow-up or patients unsuitable for analysis), the target sample size was set at 410 patients (205 per arm).

### Endpoints

The primary endpoint is 1-year major adverse cardiac events (MACE), defined as a combined endpoint of all-cause death, nonfatal MI, or unplanned target vessel revascularization (TVR). Secondary endpoints will include MACE at 2 and 5 years. Each individual component of the primary endpoint, cardiovascular death, target vessel-related and non-target vessel-related MI, all MI, clinically driven TVR or non-TVR, all revascularization, stent thrombosis, and angina symptom status will also be evaluated at 1-, 2-, and 5-year follow-up. All-cause death is defined as death of any cause, cardiovascular as well as noncardiovascular. MI is defined as a clinical episode of typical chest pain with development of new Q waves in at least two contiguous leads on an electrocardiogram or elevation of the creatine kinase myocardial band fraction (spontaneous, above the upper reference limit; periprocedural, more than three times the upper reference limit). Unplanned revascularization is defined as any unexpected coronary revascularization (PCI or CABG) during the follow-up period after the index procedure. TVR is defined as any repeat revascularization of any segment of the target vessel by either PCI (additional stent or angioplasty) or CABG. TVR will be considered to be ischemia-driven if revascularization is performed on a patient who has ischemic signs confirmed by noninvasive tests or FFR reassessment (with an inducible ischemia cutoff set at < 0.75), despite the presence or absence of ischemic symptoms. TVR will be considered to be clinically driven if revascularization is performed on a patient who has ischemic signs confirmed by noninvasive tests or FFR reassessment and clinical symptoms, such as chest pain that increases in frequency, intensity, or duration. Stent thrombosis is defined according to Academic Research Consortium definition [18]. Anginal status is assessed by Canadian Cardiovascular Society functional classification of angina. Clinical events are adjudicated by an independent and blinded clinical event committee.

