### Data collection and follow-up

The data will be collected using a web-based dedicated case report form. All data management and analysis will be performed centrally at the Department of Cardiovascular Medicine at the coordinating center (Wakayama Medical University, Wakayama, Japan). Members of the coordinating Center monitor and verify the data in the participating hospitals. Clinical follow-up will be performed during hospitalization; at discharge; and at 1 year, 2 years, and 5 years after allocation. The patient’s clinical status, medications, and adverse events will be evaluated and recorded during office visits or by qualified personnel via telephone contacts if office visits are impractical or impossible.

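### TVR, a component of the primary endpoint, is defined as repeat revascularization, so as written a first revascularization of a previously untreated vessel in the medical arm does not count

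*Protocol article*

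**What the plan says.** The Endpoints section gives the primary endpoint as 1-year MACE, "defined as a combined endpoint of all-cause death, nonfatal MI, or unplanned target vessel revascularization (TVR"). Two definitions in the same section together fix the revascularization component:

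- Unplanned: "Unplanned revascularization is defined as any unexpected coronary revascularization (PCI or CABG) during the follow-up period after the index procedure".
- TVR: "TVR is defined as any repeat revascularization of any segment of the target vessel by either PCI (additional stent or angioplasty) or CABG".

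The Randomization section names the arms: "medical therapy plus PCI group or medical therapy alone group". Only the first receives PCI of the target vessel by allocation.

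The Data collection and follow-up section schedules visits for all participants "at 1 year, 2 years, and 5 years after allocation". The definition of unplanned revascularization starts instead "during the follow-up period after the index procedure", and the protocol does not say which procedure is the index one.

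**The concern.** The TVR wording suits a trial in which every target vessel is stented at baseline. Here one arm is deferred. A first PCI of a deferred vessel that was never treated is not a repeat, and its stent is not additional to anything. An event must meet the TVR sentence as well as the unplanned one, so the literal rule leaves this revascularization out of the primary endpoint. The same rule counts a later procedure on the same vessel in the PCI arm.

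This is a stated rule, not a detail left to another document. It lowers the medical-arm rate and leaves the PCI-arm rate alone, so it biases the comparison against the superiority hypothesis. If adjudicators set the literal wording aside, the primary result rests on a reading that the protocol does not contain, in a trial that calls its open-label nature its most important limitation.

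A smaller point is the start of counting. An undefined index procedure sits beside a follow-up schedule that runs from allocation, and the two should be tied together.

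**Working it through.** **1. The wording, arm by arm**

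| Event | Unplanned sentence | TVR sentence | Counts as written? |
|---|---|---|---|
| PCI arm: later unexpected PCI or CABG of the target vessel | met | met (repeat) | yes |
| Medical arm: first unexpected PCI or CABG, vessel not treated before | met | not met | no |
| Medical arm: the same, vessel treated by PCI before the trial | met | arguably met | arguably yes |

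The third row is possible because the Exclusion criteria rule out previous CABG but not previous PCI.

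**2. The plan's own sample size**

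Inputs from Sample size calculation: "the event rates at 1 year would be 6.4% in the revascularization group and 16% in the deferred group"; 5% crossover from medical therapy alone to PCI; 80% power; two-sided alpha 5%; 184 per arm; 10% dropout. Study design gives the 1:1 ratio.

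Medical-arm rate after crossover: 0.95 × 0.16 + 0.05 × 0.064 = 0.1552. Difference: 0.1552 − 0.064 = 0.0912. Mean rate: 0.1096.

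Pooled-variance formula for two proportions, no continuity correction:

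n = [1.96·√(2 × 0.1096 × 0.8904) + 0.8416·√(0.064 × 0.936 + 0.1552 × 0.8448)]² / 0.0912²
= (1.96 × 0.4418 + 0.8416 × 0.4371)² / 0.00832 = 183 per arm.

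The plan states 184. Power at 184 is 80.2%. Dropout: 184 / 0.9 gives 205 per arm, 410 in all. The stated design reproduces and is not in question.

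**3. Sensitivity to the literal reading**

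Let f be the share of medical-arm events that are only a first target-vessel revascularization, and so are not counted. The protocol does not give f; it is an assumption, shown as a range. The PCI-arm rate is held at 6.4%.

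Counted medical-arm rate: p = 0.1552 × (1 − f), with d = p − 0.064.
Power = Φ((|d| − 1.96·se0)/se1) + Φ((−|d| − 1.96·se0)/se1), where se0 is the pooled and se1 the unpooled standard error at 184 per arm.

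Example, f = 25%: p = 0.1164, d = 0.0524, se0 = 0.0299, se1 = 0.0297. The first term is Φ(−0.21) = 0.418 and the second is negligible.

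| f | Counted medical-arm rate | Difference (points) | Power |
|---|---|---|---|
| 0% | 15.5% | 9.1 | 80% |
| 10% | 14.0% | 7.6 | 67% |
| 25% | 11.6% | 5.2 | 42% |
| 50% | 7.8% | 1.4 | 8% (7% in favour of PCI) |
| 59% | 6.4% | 0 | 5%, the false-positive level |

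The difference is zero at f = 1 − 0.064/0.1552 = 58.8%. Above that the counted rates favour the medical arm. With the undiluted 16% the crossing point is 1 − 0.064/0.16 = 60%.

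**The case against.** The strongest reply is that nobody would read the section this way. The definition of unplanned revascularization has no repeat condition. The ischemia-driven and clinically driven definitions speak simply of revascularization being performed, and both allow FFR reassessment, which suits a deferred vessel. The sample size expects more events in the deferred arm. All this stands as evidence of intent, and it is why the point is a wording defect and not a forecast that events will be lost. It does not cure the text: the primary component is unplanned TVR, the repeat condition sits in the TVR sentence, and the two finer definitions only sub-classify TVR.

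Three stronger inferences are tempting, and the protocol does not support them.

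- *That the excluded events are the main events of the medical arm, or those the trial was sized on.* The 16% is not split by component anywhere.
- *That every medical-arm target vessel is untreated.* Previous PCI is not an exclusion, so some first in-trial revascularizations might qualify as repeat.
- *That the two arms run on different clocks.* Follow-up runs from allocation for everyone, and the index procedure can be read as the angiography and FFR procedure that both arms undergo. Different origins arise only if it means the assigned PCI. Their effect then depends on a delay between allocation and PCI that the protocol does not state. At the 16% rate the hazard is −ln(0.84) = 0.174 per year, so the risk in the gap is zero for same-session PCI, 1 − exp(−0.174 × 7/365) = 0.3 points for an assumed 7 days and 1.4 points for an assumed 30 days. Even these overstate it, because they use the whole MACE hazard while the index-procedure wording governs revascularization only.

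**Conclusion.** The point holds as a defect in the definition of a primary-endpoint component. As written, a first PCI or CABG of a previously untreated target vessel in the medical arm does not count, while any later revascularization in the PCI arm does.

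The size is conditional. It depends on adjudicators applying the literal text and on an undocumented share of medical-arm events. It also assumes a PCI-arm rate fixed at 6.4% and a simple comparison of proportions. Within those limits a modest share matters: excluding one event in ten lowers power from 80% to about 67%, and one in four to 42%. The documents do not show that such a loss will occur.

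The undefined index procedure is a minor, separate gap in drafting. It is not evidence of unequal follow-up. Neither matter alters the stated sample size.

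**What to change.** Replace the TVR sentence with one that fits both arms: TVR is any unplanned PCI or CABG of any segment of the target vessel after randomization, in either arm, whether or not that vessel was treated before, other than the initial PCI assigned by randomization.

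Add a second sentence making randomization time zero for every endpoint in both arms, and drop or define the index procedure accordingly. Put the same text in the event committee's charter.

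The cost is two sentences. No further data or patients are needed, and 184 per arm (205 with dropout) stands. The Trial status section says that recruitment has not yet opened, so the change can be made before the first patient is enrolled.

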### Coronary angiography

Coronary angiography will be performed in the standard manner via a transradial or transfemoral approach in each center. Intracoronary (IC) isosorbide dinitrate or nitroglycerin is administered in all cases preceding coronary angiography. A coronary angiogram is obtained from a standard series of six to eight projections for the left coronary artery and two or three projections for the right coronary artery. All images are stored on a CD-ROM for offline analysis. Diameter stenosis, minimum lumen diameter, lesion length, and reference lumen diameter will be measured by using dedicated software for quantitative coronary angiography (CASS-5; Pie Medical, Maastricht, The Netherlands). Quantitative coronary angiographic analysis is conducted at the Core Laboratory of Wakayama Medical University, Wakayama, Japan.

### FFR measurement

IC pressure will be measured using a pressure wire system (PressureWire, Abbot Vascular, Santa Clara, CA, USA; Smartwire, Philips Volcano, San Diego, CA, USA; Comet, Boston Scientific, Marlborough, MA, USA; or OptoWire, Zeon Medical, Tokyo, Japan). FFR measurement will be done as reported previously [17]. In brief, following pressure zero-calibration and equalization, the pressure wire will be placed in the distal part of the target coronary artery. IC nitroglycerin is administered prior to FFR measurement. FFR is calculated as the mean distal coronary pressure, measured by the pressure wire, divided by the mean aortic pressure, simultaneously measured by the guiding catheter during maximal hyperemia. Maximal hyperemia will be induced by intravenous continuous infusion of adenosine 5′-triphosphate (ATP), given at 180 μg/kg/min via the forearm or femoral vein. If maximal hyperemia is suspicious, additional IC papaverine (12 mg for left coronary artery or 8 mg for right coronary artery), IC nicorandil (2 mg for both coronary arteries), or IC ATP (50 μg for left coronary artery or 25 μg for right coronary artery) administration will be recommended. In case of contraindication to ATP, IC papaverine or IC nicorandil should be administered alternatively. After distal pressure measurement is done, the pressure sensor is pulled back to the ostium of the guiding catheter during maximal hyperemia, and both pressures are checked to exclude any transducer drift. Where drift is evident (Pd/Pa < 0.98 or > 1.02 measured at the level of the catheter tip), measurements should be repeated. Because caffeine attenuates ATP-induced hyperemia by blocking activation of adenosine A2a receptor in vascular smooth muscles, patients should refrain from consuming products containing caffeine 24 h (at least 12 h) before FFR measurement [19, 20].

### PCI

In the medical therapy plus PCI group, PCI will be performed in the standard manner according to clinical guidelines at the time of the procedure by using currently available second-generation or third-generation drug-eluting stents (DES). The choice of approach site (transradial or transfemoral) is at the operator’s discretion. Also, the type of DES and the use of intravascular imaging are at the discretion of the operator. Patients who underwent PCI will be treated with aspirin (100 mg/day) and thienopyridines (clopidogrel 75 mg/day or prasugrel 3.75 mg/day) for at least 6 months, followed by aspirin indefinitely.

### Medical therapy

Guideline-directed optimal medical therapy will be applied to all participants, regardless of the treatment arm.

### Data collection and follow-up

The data will be collected using a web-based dedicated case report form. All data management and analysis will be performed centrally at the Department of Cardiovascular Medicine at the coordinating center (Wakayama Medical University, Wakayama, Japan). Members of the coordinating Center monitor and verify the data in the participating hospitals. Clinical follow-up will be performed during hospitalization; at discharge; and at 1 year, 2 years, and 5 years after allocation. The patient’s clinical status, medications, and adverse events will be evaluated and recorded during office visits or by qualified personnel via telephone contacts if office visits are impractical or impossible.

### Safety monitoring

Safety is observed throughout the study. During the study period, all participants will be monitored and evaluated for clinical events and any other adverse events by the data and safety monitoring committee.

### Statistical analysis

Continuous variables will be summarized as mean ± SD or median (IQR) for skewed data, and comparisons will be made using an unpaired Student’s *t* test or Mann-Whitney’ *U* test as appropriate. Categorical variables will be summarized as number (%), and comparisons will be made using the chi-square test or Fisher’s exact test as appropriate. Kaplan-Meier survival analysis curves will be used to assess clinical event timelines and will be compared with the log-rank test. Also, in time-to-event analyses, the treatment groups will be compared using a Cox proportional hazards model, and the results will be expressed as an HR with 95% CI. Values of *p* < 0.05 will be considered statistically significant. All statistical analyses will be conducted using JMP Pro version 14 software (SAS Institute, Cary, NC, USA).

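### Angina status is graded on an ordered scale, but the only rule stated for categorical data is an unordered test without an effect estimate

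*Protocol article*

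**What the plan says.** The Endpoints section places angina among the outcomes that follow the primary endpoint: "stent thrombosis, and angina symptom status will also be evaluated at 1-, 2-, and 5-year follow-up". It fixes the scale: "Anginal status is assessed by Canadian Cardiovascular Society functional classification of angina". It does not say how many levels will be used or whether they will be grouped.

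The Statistical analysis section gives methods by type of variable:

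- Categorical: "Categorical variables will be summarized as number (%), and comparisons will be made using the chi-square test", or Fisher's exact test where appropriate.
- Continuous: "Continuous variables will be summarized as mean ± SD or median (IQR) for skewed data", compared by Student's t test or the Mann-Whitney test. This is the only place where a rank test is named.
- Event times: Kaplan-Meier curves, the log-rank test and a Cox model. A hazard ratio with 95% CI is promised here and nowhere else.

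No trend test, ordinal model or baseline adjustment is mentioned, and no sentence names the test for CCS class.

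**The concern.** CCS classes run from less to more angina. A chi-square or Fisher test on the full table gives the same p value if the class labels are shuffled. It therefore spends 3 degrees of freedom (four classes) or 4 (five classes) on what would most plausibly be a shift in one direction. The stated rule also yields no effect estimate with a confidence interval for this endpoint and makes no use of the baseline class.

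The trial compares PCI with medical therapy in stable angina patients, so symptom status will matter to readers even though the stated objective is cardiovascular events. A moderate but real shift in angina could be reported as not significant, without an interval to show what size of effect remains compatible with the data.

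**Working it through.** **1. The plan's own figure.** The sample size rests on the primary endpoint: "the event rates at 1 year would be 6.4% in the revascularization group and 16% in the deferred group". With 5% crossover the deferred rate becomes 0.16 − 0.05 × (0.16 − 0.064) = 0.1552. The pooled-variance formula for two proportions (two-sided 5%, 80% power) gives 183 per arm against the stated 184. Power at 184 is 80.2%. Then 184 / 0.90 = 204.4, so 205 per arm and 410 in total. The figure reproduces, and nothing below changes it. No power, effect size or class distribution is stated for angina.

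**2. Inputs for the angina check.**

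- From the protocol: 184 per arm, two-sided 5%.
- Assumed: four or five levels, the medical-arm distributions in the table, and a proportional-odds shift with common odds ratio (OR) 1.5 to 2.0.

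**3. Formulas.** Let p0 and p1 be the class proportions by arm, p̄ their mean, k the number of classes and n = 184.

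- Unordered test: noncentrality λ = n Σ (p0 − p1)² / (2p̄), on k − 1 df.
- Rank test: midrank scores r (cumulative p̄ minus p̄/2) with variance v, and λ = n [Σ r(p1 − p0)]² / (2v), on 1 df.
- Power is the upper tail of the noncentral chi-square beyond the 5% critical value.

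**4. Worked example.** Take 50/20/20/8/2% in the medical arm and OR 1.75. The PCI arm becomes 63.6/16.7/13.7/4.8/1.2%. Both statistics have λ = 7.60. The unordered test must exceed 9.49 (4 df) and has 58% power. The rank test must exceed 3.84 (1 df) and has 79%. Splitting at the lowest class (50% v 63.6%) gives λ = 6.97 and 75%.

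**5. Range.** Loss in percentage points against the rank test:

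| Medical-arm classes (%) | Unordered, OR 1.5 | OR 1.75 | OR 2.0 | Split at lowest class, OR 1.5–2.0 |
|---|---|---|---|---|
| 85/10/4/1 | 8.6 | 13.4 | 16.2 | 0.1 |
| 75/15/8/2 | 12.2 | 16.5 | 16.6 | 0.4–0.5 |
| 60/25/12/3 | 15.0 | 16.7 | 12.8 | 1.0–1.6 |
| 50/20/20/8/2 | 19.8 | 20.8 | 14.4 | 2.0–3.9 |
| 40/25/20/10/5 | 20.5 | 19.9 | 12.3 | 3.3–7.1 |

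At OR 1.7 the loss for 50/20/20/8/2 is 21.5 points, the largest found. With 62/22/13/3 and OR 1.7, power is 50% unordered against 67% for the rank test. The loss from splitting grows as fewer patients fall in the lowest class: with 30/30/25/10/5 it is 6 to 12 points.

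**6. In patients.** For 80% power λ must be 7.85 on 1 df, 10.90 on 3 df and 11.94 on 4 df. Under a consistent shift λ is nearly the same for both tests, so the unordered test needs 10.90/7.85 = 1.39 or 11.94/7.85 = 1.52 times as many patients.

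**7. Baseline class.** In simulations (2,000 trials each, 184 per arm, assumed latent correlation 0.3 to 0.5), adjusting ranks for baseline class raised power from 51% to 53% and from 53% to 61% at OR 1.5, and from 78% to 81% and from 78% to 85% at OR 1.75. That is a gain of about 2 to 8 points.

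**The case against.** The strongest reply is that the categorical rule is a generic sentence in a condensed article. It does not mention angina, and the analysis of one secondary endpoint may be set out in an analysis plan that is not shown. CCS could be compared in full classes, split into two, or treated as a score.

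Much of this stands. A reader might infer that chi-square on the full classes is the settled analysis, or that a large part of the power is certainly thrown away. The protocol supports neither reading: no sentence assigns the test to CCS class, and it gives no class distribution, effect size or correlation. The proportional-odds shift also favours ordered tests by construction, and if the effect were not a consistent shift the ranking of the tests could reverse.

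Three further readings also go too far:

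- That the rule shows no direction of effect. Percentages by arm do show it; what is missing is an estimate with an interval.
- That ignoring baseline class biases the comparison. Under randomization it costs only precision.
- That baseline CCS is available for adjustment. The schedule is in a figure that is not shown, so this cannot be confirmed.

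Treatment is open-label as well, and no choice of test removes expectation bias in symptom grading.

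What does not stand is the claim that this is only missing detail. The article states a rule for categorical data and names a rank test for continuous data alone. Read as written, class data fall under the unordered rule.

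**Conclusion.** The point holds conditionally and is minor. If the stated categorical rule is applied to the full CCS classes, it ignores their order and leaves the endpoint without an effect estimate and confidence interval. The loss of roughly 8 to 22 percentage points rests entirely on assumed class distributions, a consistent shift with common odds ratio 1.5 to 2.0, and 184 patients per arm. It becomes small if CCS is split at the lowest class and that class holds at least about 40% of the medical arm. The gain from baseline adjustment is a few points and depends on an assumed correlation. The primary comparison and the sample size do not depend on any of this.

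**What to change.** Add one sentence to the Statistical analysis section: CCS class at 1, 2 and 5 years will be compared with an ordinal analysis, adjusted for baseline CCS class where recorded, reporting the common odds ratio with 95% CI. Name the proportional-odds model as the main method, with a rank test if proportional odds is doubtful or cells are sparse. Keep the cross-tabulation of numbers and percentages as description.

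The cost is small, since the article says recruitment has not yet opened. The downside is that the proportional-odds assumption must be checked with few patients in the higher classes: at an assumed 3%, the top class would hold about 0.03 × 184 = 5.5 medical-arm patients, so the check will be weak.
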